### Objectives

We hypothesise that comprehensive cardiac rehabilitation after heart valve surgery compared with treatment as usual [7,25,26] improves physical capacity (at 4 months) measured by peak VO_2_ (oxygen uptake) by >3 mL/kg/min (primary outcome) [6,10,14,15,20,21,27], and improves self-rated mental health (at 6 months) measured by Short Form 36 (SF-36), the mental health component scale (secondary outcome) by 7 points [28,29]. The reason for choosing separately assessed outcome times is due to the different durations of the two intervention elements; the exercise training is undertaken until 4 months post surgery and the psycho-educational intervention until 6 months post surgery. Further, the physical recovery is expected to be faster than the mental recovery and therefore not comparable.

In exploratory analyses we will assess the effects of integrated rehabilitation *versus* treatment as usual on a 6-minute walk test, heart specific biomarkers (pro-brain natriuretic peptide and copeptin [30]), and echocardiographic measurements (diastolic function (E/A ratio), left atrial size (mm), left atrial volume (mL)) [31,32]. Furthermore, we will assess the effects on time to return to work after valve surgery, and long-term (24 months) employment resignation [5,6,33], healthcare utilisation and mortality [8], and cost effectiveness [33]. Standardised questionnaires: Hospital Anxiety and Depression Scale [HADS] [34], Quality of life Cardiac Version [QoL-CV], EQ-5D [35], Heart Related Quality of Life [HeartQoL R] [36], International Physical Activity Questionnaire [IPAQ] [37], physical activity score and the Emotion and Health Scale [38] will be applied to ascertain numerous exploratory hypotheses concerning the possible effects of rehabilitation on patient perceived physical and mental health.

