### Participants

The trial is planned to include approximately 210 participants of both sexes admitted to hospital for isolated heart valve surgery.

Inclusion criteria are: patients admitted to hospital for elective right-or left-sided heart valve surgery; age ≥18 years; speak and understand Danish; and informed written consent.

Exclusion criteria are: known ischemic heart disease prior to surgery, due to the documented effect of rehabilitation in patients with ischemic disease [8,43]; recruited to other trials including physical exercise and psycho-educational intervention, and participating in other trials inhibiting participating in the present trial; failure to understand and cooperate according to the trial instructions; diseases in the musculoskeletal system or other organs complicating physical activity and exercise training; individuals performing hard physical exercise and competitive sports several times weekly; pregnant and/or breast-feeding women; and lack of informed consent.

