#### Exploratory outcome measures

Register-based follow-up. Register data regarding mortality, causes of death, hospitalisation/re-hospitalisation, emergency room visits, outpatient visits, healthcare costs, visits to the general practitioner, medication use, employment status, and payment of welfare benefits (sick leave payment and early retirement pension) will be collected at 24 months to assess the long-term effect of the intervention (Table 1). Danish registers for the data mentioned above function well with only a small percentage of lost data [62]. Consequently the method is well suited as an outcome measure in small patient populations. Data will be extracted from the Danish National Patient Register [63], the Danish National Health Service Register [64], the Danish National Prescription Registry, the Danish National Causes of Death Register [65], and records of transfer payments and labour market affiliation [66,67].

Furthermore, the outcomes below will be measured at 1, 4 and 12 months following randomisation (Table 1). Questionnaires are also distributed at 6 and 24 months.

Six-minute walk test. The maximum walking distance (in meters) within 6 min is measured using standardised instructions [44], while subjective exhaustion with regard to fatigue and dyspnoe before and after using the Borg scale [55] is recorded.

Sit and stand test. The maximum number of times a patient can sit and rise from a normal chair within 30 s. Rate of perceived exertion is measured before and after using the Borg scale.

Biochemical screening. C-reactive protein (CRP), urea, glucose, haemoglobin, HbA1c, potassium, sodium, total cholesterol, creatinine, HDL cholesterol, LDL cholesterol and triglycerides. 1 EDTA plasma heparin tube will be frozen (80°) for further analyses (pro-brain natriuretic peptide and copeptin). The rationale for measuring cholesterol and triglyceride levels is to explore risk markers for cardiovascular disease for this patient group.

Questionnaires. The patient’s perceived physical and mental health will be analysed using relevant standardised questionnaires as mentioned in the objectives section (SF-36, HADS, QoL-CV, EQ-5D, HeartQoL, IPAQ and Emotion and Health Scale).

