mis, mis, Y3^e^	Y3 - (delta^f^ + delta2^g^)^h^	Y3 - delta2	
mis, Y2, mis	Y2 – delta1		Y2 + delta2
Y1, mis, mis		Y1 + delta1	Y1 + delta1 + delta2
Y1, Y2, mis			Y2 + delta2
Y1, mis, Y3		(Y1 + delta1 + Y3 -delta2)/2	
mis, Y2, Y3	Y2 - delta1		

Table to explain the use of imputing quantities derived from observed values in a group (group A) to impute missing values in a group (group B).

^a^The value at 4 months is missing in group B.

^b^Mean of values observed in group A at 1 month.

^c^Mean of values observed in group A at 4 months.

^d^Mean of values observed in group A at 6 months.

^e^Observed value in group B at 6 months.

^f^The mean of difference between values observed at 4 months and value observed at 1 month in group A.

^g^The mean of difference between value observed at time 6 months and value observed at time 4 months in group A.

^h^If an imputed value is 0 it is set equal to 0.

Mis, Missing value; X1, Value at month 1; X4, Value at month 4; X6, Value at month 6.

Long-term register-based follow-up will be analysed by two different models: non-negative count outcomes (for example, number of contacts to hospital or number of visits to general practitioners) will be analysed by a Poisson model or a zero-inflated Poisson model if the number of zeros are large, and time-to-event data (for example, mortality and leaving the labour market) will be analysed with survival methods (Kaplan-Meier estimator and Cox regression model). Especially for socioeconomic outcomes, competing risks due to mortality will be considered if a large proportion of patients die during follow-up.

Exploratory outcome measures including data from the 6-minute walk test, ‘sit and stand’ test, biochemical screening and echocardiography will be analysed using appropriate statistical methods.

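### The competing-risk rule for register outcomes names only death, conditional on an undefined share dying; for time to return to work it should also cover permanent labour-market exit

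*Protocol article*

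**What the plan says.** The Objectives section of the protocol lists, among the exploratory analyses: "we will assess the effects on time to return to work after valve surgery, and long-term (24 months) employment resignation".

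Under Exploratory outcome measures, the register-based follow-up states that "employment status, and payment of welfare benefits (sick leave payment and early retirement pension) will be collected at 24 months". Mortality and causes of death come from registers as well.

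The Statistical analysis section gives the method for long-term register data: "time-to-event data (for example, mortality and leaving the labour market) will be analysed with survival methods (Kaplan-Meier estimator and Cox regression model". It then adds the only sentence on competing risks: "Especially for socioeconomic outcomes, competing risks due to mortality will be considered if a large proportion of patients die during follow-up".

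Return to work is not named in the Kaplan-Meier sentence. The two outcomes that are named are introduced as examples. The section does not say how a patient who permanently leaves the labour market before returning is to be treated in a return-to-work analysis.

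**The concern.** Two events prevent a patient from returning to work: death, and permanent exit from the labour market. The protocol recognises the first, conditionally, and records the second, but treats exit only as an outcome in its own right and never as an event that competes with return.

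The condition does not help. However common exit is, a rule triggered by the number of deaths cannot respond to it. The trigger also has no stated threshold, so nobody can tell in advance whether competing-risk methods will be used.

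What is at stake is the absolute proportion returning to work by 24 months. If patients who exit are censored, Kaplan-Meier assumes that they would have gone on to return at the same rate as those still on sick leave, and the curve is then too high. The Discussion section itself attaches weight to social and community outcomes because little is known about them in these patients, so the reported percentages may be used.

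**Working it through.** **What the protocol supplies.** It gives no rate for return to work, labour-market exit or death, and no number of participants in the labour market before surgery. There is no figure to reproduce, and every rate below is an assumption.

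**Does the general rule reach return to work?** Time to return to work is time-to-event data by definition, and the employment and sick-leave data come from registers. The Kaplan-Meier and Cox rule is general, with examples. That it covers return to work is a fair inference, though not an explicit statement.

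**Formula.** Take constant cause-specific hazards over 24 months. Let the true 24-month cumulative incidences be r (return), e (exit) and d (death), with total p = r + e + d.
- Total cumulative hazard: L = −ln(1 − p)
- Cumulative hazard of return: A = L × r/p
- One minus Kaplan-Meier, with exit and death censored: 1 − exp(−A)

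**Example, 80% return and 10% exit or die first.** p = 0.90, so L = −ln(0.10) = 2.303. A = 2.303 × 0.80/0.90 = 2.047. Then 1 − exp(−2.047) = 0.871, which is 87.1% against a true 80%, or 7.1 points too high.

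| True return | Exit or death first | 1 − KM | Excess (points) |
|---|---|---|---|
| 85% | 5% | 88.6% | 3.6 |
| 80% | 10% | 87.1% | 7.1 |
| 75% | 15% | 85.3% | 10.3 |

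For scale, the standard error of 80% is sqrt(0.8 × 0.2/n): 3.9 points if all 105 patients in an arm were in the labour market, and 6.3 points if only 40 were.

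**Exit and death separated: r = 70%, e = 10%, d = 2%.** L = −ln(0.18) = 1.715, so the cumulative hazards are 1.464 (return), 0.209 (exit) and 0.042 (death).
- Both censored: 1 − exp(−1.464) = 76.9% (+6.9 points).
- Death competing, exit censored (what the mortality clause would give if triggered): (1.464/1.506) × (1 − exp(−1.506)) = 75.7% (+5.7 points).
- Exit competing, death censored: (1.464/1.673) × (1 − exp(−1.673)) = 71.1% (+1.1 points).

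Here the mortality clause removes about 1.2 of the 6.9 points.

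**Range.** For return of 50, 60, 70 or 80%, exit of 2, 5, 10 or 15%, and death of 2%, the excess with both censored runs from 1.3 to 14.5 points. Fourteen of the 16 combinations lie between 1 and 10 points; the other two (15% exit with 70% or 80% return) give 10.6 and 14.5. With only exit censored, the range is 0.6 to 12.5 points.

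**Timing.** The hazards below are monthly, first for months 0–6 and then for months 6–24, with a death hazard of 0.002 throughout.
- Return 0.15 then 0.03, exit 0.002 then 0.02: true return 72.7%, 1 − KM 76.3% (+3.6 points; 10.1% exit).
- Return 0.20 then 0.01, exit 0.001 then 0.02: true return 73.4%, 1 − KM 74.8% (+1.4 points; 8.4% exit).

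**If exits are not censored.** When patients who exit stay at risk as not returned to 24 months, the excess due to exit is nil.

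**What the hazard ratio shows.** Take a return hazard of 1.0 per year in both arms and an exit hazard of 0.2 against 0.1 per year, over two years.
- True return: (1.0/1.2) × (1 − exp(−2.4)) = 75.8% against (1.0/1.1) × (1 − exp(−2.2)) = 80.8%, a difference of 5.1 points before rounding.
- 1 − KM with exits censored: 1 − exp(−2) = 86.5% in both arms. The cause-specific hazard ratio for return is 1.

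**Leaving the labour market, with death competing.** Assume 20% leave. With 3% dying, A = −ln(0.77) × 0.20/0.23 = 0.227 and 1 − KM = 20.3% (+0.3 points). With 10% dying, A = −ln(0.70) × 0.20/0.30 = 0.238 and 1 − KM = 21.2% (+1.2 points).

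**The case against.** The strongest reply is that the protocol contains no wrong statement here. It never says that exits are censored. It does not expressly assign Kaplan-Meier to return to work. For the socioeconomic outcome it does name, leaving the labour market, death is the natural competing event and ignoring it costs little. The outcome is exploratory, and the detail of censoring is commonly left to an analysis plan, which is not shown. All of this stands, and it limits the point to a minor one. It does not remove it: the article does state a competing-risk rule for socioeconomic outcomes as a class, and that rule is incomplete for return to work and has no defined trigger.

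A reader might infer three stronger claims that the documents do not support.
- *Kaplan-Meier will overstate return to work.* This follows only if exits are censored, which is not stated.
- *A benefit of rehabilitation would be hidden.* In the contrast above, the hazard ratio of 1 is the correct cause-specific ratio for return, and fewer exits would show in the separately planned analysis of leaving the labour market. What would be missing is the difference in the proportion who return.
- *The estimator is chosen on the results.* The trigger is the proportion of patients who die, not a difference between arms, and the analysis is done blinded by a trial-independent statistician. The fair criticism is that the threshold is undefined.

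The sizes can also be challenged. Constant hazards give larger values than early return with late exit. There is no upper age limit ("patients admitted to hospital for elective right-or left-sided heart valve surgery; age ≥18 years"), so the number in the labour market may be well below 105 per arm, and any bias would then be smaller relative to the standard error.

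**Conclusion.** The point holds as a minor one. The stated rule considers only death as a competing event, and only if an unspecified large share die. For time to return to work, permanent labour-market exit also precludes the event, and the rule cannot detect it. If exits are censored, the reported proportion returning would be too high, by about 1 to 10 points in most of the assumed scenarios, by about 1.4 to 3.6 points in the two runs with early return and late exit, and by nothing on account of exit if these patients stay at risk as not returned. These sizes rest wholly on assumed rates. The Cox model remains valid as a cause-specific hazard ratio but does not say how many patients return. For leaving the labour market the effect of ignoring death is small, about 0.3 to 1.2 points under assumed rates.

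**What to change.** Replace the conditional sentence in the Statistical analysis section with a fixed rule:
- **Return to work**, among patients in the labour market before surgery: report Aalen-Johansen cumulative incidence by arm, with permanent labour-market exit and death as competing events.
- **Leaving the labour market:** do the same, with death as the competing event.
- **Cox models:** keep them, shown alongside and labelled as cause-specific hazard ratios.
- **All-cause mortality:** keep Kaplan-Meier.

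The cost is a change of wording, a little extra code, and return-to-work percentages slightly lower than Kaplan-Meier with censored exits would give. Dates of return, exit and death must also be extracted. Table 1 shows register-based employment status only as a categorical item at 24 months, so the data request should ask for event dates explicitly.

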### Sample size and power calculation

We are performing a randomised trial with the continuous variable VO_2_ peak from independent control and intervention group participants as primary outcome with one control per intervention group participant. Previous studies report that VO_2_ peak is normally distributed in the intervention and control groups with a standard deviation between 4.0 and 9.3 mL/kg/min [14,15,20,21], though this might depend on the baseline peak VO2. However, if the true difference between the intervention and control group mean is 3 mL/kg/min [14,15,21], and the standard deviation is 6 mL/kg/min, inclusion of 105 participants is needed in the experimental intervention group, and 105 in the control group (a total of 210 participants) to be able to reject the null hypothesis, stating that the mean in the intervention and the control groups are the same with a power of 95%, and a type I error probability of 5%.

The secondary outcome measure is the continuous variable ‘mental health’. If the true difference between the intervention and control group is 7 points, and the standard deviation is 18 points [28,29], we will be able to reject the null hypothesis that the population means in the intervention and control group are equal with a probability of 80%, and a type 1 error probability of 5%.

## Discussion

The major strength of The CopenHeart_VR_ is that it includes consecutive patients with a reasonable number of inclusion and exclusion criteria securing external validity for the results. The trial employs central, stratified randomisation, which secures against selection bias [77-79]. The primary outcome is assessed blinded to intervention, and so are all statistical analyses, which should reduce detection and interpretation bias [77-79]. The long-term outcomes are based on registry data, which are also likely not to include significantly biased reporting of outcomes.

The secondary outcome of self-assessed mental health is by nature subjective, and is likely to be biased [77-79]. The patients answer questionnaires independently of the researchers. All questionnaires are distributed electronically, thus data management is handled independently from the researchers that interpret data. All data are stored electronically in a coded database, and in an independent spread sheet, only accessible for the CopenHeart Group. The exploratory outcome measures highly impact the importance of this study as very limited knowledge exists concerning social and community outcomes for this patient group.

The limitations of the trial and methods used are similar to those of other trials including physical exercise and physical testing, which are time-of-day, and day-to-day variation in exercise testing [80]. To ensure standard testing of all physical exercise tests in the trial, standardised instructions for patients have been developed as described in the methods section. Including trial patients with left- and right-side heart valve surgery will result in an inhomogeneous trial population. Also, as peak VO2 is dependent on exercise capacity, age or recovery capacities, which differ according to the valve involved, consequently the expected results are going to depend on the recruitment. Conversely, the trial population will be representative of the broad heart valve population, and facilitate the external validity of The CopenHeart_VR_ rehabilitation programme in terms of daily clinical practice.

The fact that patients have different options for their intervention (home-based training, municipal setting or continuous training at a heart centre in hospital setting), and that the effect of the three different settings for training are unknown, might influence the exercise training, and thus the intervention, the primary and secondary outcome and exploratory analyses. However, patient compliance may be increased with different options, and supervised home-based training for cardiac patients has previously shown effective results compared to centre-based training [52,81].

Finally, it has been shown that a substantial number of patients allocated to the control group of a randomised rehabilitation trial perform self-initiated physical exercise training, possibly motivated by the trial information during the recruitment process [82,83].

To conclude, The CopenHeart_VR_ will be unique in obtaining information on the organisation of rehabilitation across sectors, and on how to optimise the transition phase after hospital discharge in order to initiate and provide rehabilitation more rapidly, after heart valve surgery. This is in accordance with current strategies for future healthcare organisation as suggested by the World Health Organization [84]. It is expected that results from the trial will contribute to the development of heart valve specific clinical rehabilitation guidelines, and to identify requirements for resources within the field.

### Safety aspects and Data Monitoring Safety Committee (DMSC)

In supervised exercise training and testing of cardiac patient groups other than post heart valve surgery, the risk of adverse effects is low (for example, ischemic heart disease, chronic heart failure), however, no current national safety instructions exist. Patient safety is given the highest priority, and exercise training after heart valve surgery is considered safe based on results from exercise testing and training with heart failure patients [85,86]. Any serious adverse events will be registered as part of the data collection.

The DMSC works independently from the funder and has no competing interests, and consists of two clinicians and a statistician. The committee is responsible for safeguarding the interests of trial participants, assessing the safety and efficacy of the interventions during the trial, and for monitoring the overall conduct of the clinical trial. The steering committee and the DMSC communicate regularly, and at least every 9 months the overall number of all serious adverse events is reported.

## Trial status

The duration of inclusion is fixed at a maximum of 2 years to minimise the influence of changing treatment trends on usual care intervention over time, and for trial organisational reasons. Based on current activity levels of valvular surgery at the Heart Centre, Rigshospitalet, this can be achieved with an inclusion proportion of 35%. To achieve adequate participant enrolment, patients in doubt are contacted after hospital discharge by phone, and another heart centre that is already in partnership with the trial will be invited to participate if the enrolment rate declines. The inclusion rate is carefully monitored every week.

Results of the trial and complementary studies will be published in relevant international peer-reviewed journals. Authorship will be determined according to the guidelines of the International Committee of Medical Journal Editors. Due to the comprehensiveness of the outcomes the results will be presented in more than one scientific paper as relevant. Economic and long-term follow-up will be reported as data become accessible. Continuously updated information about the trial is available at http://www.copenheart.org/.

## Conclusion

This randomised clinical trial, The CopenHeart_VR_, will be the first trial to investigate the effect of an individually tailored comprehensive cardiac rehabilitation programme comprising physical exercise and a psycho-educational intervention aimed at a broad group of patients after isolated heart valve surgery in a municipal, hospital or home-based setting. Due to its size, positive, negative or neutral outcomes from The CopenHeart_VR_ are likely to have an impact on the organisation of and clinical guidelines for future rehabilitation after heart valve surgery.

